There is a shortage of literature evaluating the effects of PT in ED for non-musculoskeletal chief complaints [20]. Data from our hospital [21] and from Gurley et al. [22] reported that ‘falls’ in older populations might account for up to 40% of PT prescriptions [21] or interventions [22] within the ED. Another retrospective study also emphasized the potential for delivering PT in the ED to ‘fallers’ [23]. However, this study did not allow for an estimation of the specific nature of PT service provided (e.g. assessment and/or therapeutic sessions; location within the ED units) or the effects produced on patient discharge and length of stay.

The number of patients aged 75 years and over presenting to the ED increasing, so as their primary complaint identified as ‘fall’ [6,24–26]. It is also estimated that more than 50% of fall patients presenting at the ED report adverse events: recurrent falls, revisits to the ED with subsequent hospitalisations within 6–12 months [27,28], and up to 15% mortality rate one year later [28]. Given the challenges in caring for the elderly population due to frailty and their higher risk for adverse outcomes after an ED visit, there is a need for special attention on screening/assessment and strategies offered to this population in ED [11,29]. To the best of our knowledge, no study has prospectively estimated the effect of delivering PT to patients aged 75 and over admitted in ED with a chief complaint of ‘fall’.

Therefore, the main objective of this study is the evaluate the effect of delivering PT in the ED (versus no PT) in patients aged 75 years and over for ‘falls’ complaints, on the discharge disposition after their ED visit.

The secondary objectives are to evaluate the effect of the intervention (PT vs no PT) on:

the length of stay (LOS) within the ED and the hospitalthe number of falls recorded within the 7 days after admission in EDthe medical staff satisfaction of PT practice in EDthe changes between initial and final EP decision regarding patient orientation (discharge home, acute care unit, hospitalization)

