### Study setting

This study will be conducted in the adult ED of University Hospital (CHU) of Nantes between April 6, 2023 and February 29, 2024. This ED is one the largest in France, with an average of 219 daily visits and a total of 78 908 annuals visits reported in 2021 (adult ED). Among these patients, 14.0% are aged over 75 years (national rate: 13.9%) [6,31].

The ED is divided into different sectors (traumatic, non-traumatic, fast-track, resuscitation room). Following an initial triage by a specialized nurse, patients are directed to one of the aforementioned sectors based on their clinical presentations and severity. Then, at the Emergency Unit (EU), the Emergency Physician (EP) conducts an initial clinical exam leading to: i) an initial course of action, including prescription (medical imaging, clinical investigation/assessments, biological analyses), and/or introduction of treatment; ii) and an initial decision for patient orientation depending on the clinical severity, treatment requirement, and the initial evolution of the patient. This may include decisions such as a hospital admission, discharge with follow-up instructions, or referral to outpatient specialist. Another possibility is to admit the patient to an Observation Unit (OU) that is close to the ED. The OU is dedicated for the surveillance after initial clinical examination of patients with unpredictable evolution. For instance, if the evolution indicates a more severe condition than initially thought, the EP can decide to admit the patient to the hospital instead of sending him home (discharge). Similarly, if the condition significantly improves with the introduction of treatment, the initial decision for hospital admission can be re-evaluated [32].

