Briefly, patients aged 75 years and over admitted with a chief complaint of a ‘fall’ are first clinically assessed within the EU, to provide a prompt clinical exam, an initial course of action, and an initial decision for orientation. After this first stage, there are three possibilities: (i) the situation is benign and the patient is discharged; (ii) there is a clear indication for hospitalization; or (iii) the clinical situation is unpredictable and the patient can be admitted to the OU for observation/monitoring, treatment, and further assessments. As illustrated in Fig 3, the typical pathway involves patients initially going to the EU where they may be directed to one of the three options: returning home, being hospitalized (in another unit of the hospital), or being transferred to the OU. Once in the OU, these patients may later be directed to either return home or continue hospitalization.

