### Allocation

Participants will be randomly allocated to either study group: PT or no-PT with a ratio 1:1. A SAS program will be used to produce a permuted blocks randomization plan with varying block sizes. This program will be performed by a statistician of the DRI of the University Hospital of Nantes. The randomization will be not stratified.

The investigator can allocate the study group of the included patients using a web browser by connecting to ENNOV Clinical Software: this is a secure, computer-generated, interactive web-response system available at: https://nantes-lrsy.ennov.com/EnnovClinical/login.

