### Outcomes

All outcomes, measurement time points and aggregations methods are described in Table 2.

**Table 2 pone.0303362.t002:** Summary of outcomes.

Variable	Aggregation method	
	‘PT-group’	‘no PT-group’
Age, at ED admission	mean (SD)	
Gender		
female	n (%)	
male	n (%)	
Emergency Severity Index Level		
1	n (%)	
2	n (%)	
3	n (%	
4	n (%)	
5	n (%)	
Average	mean (SD)	
Primary diagnosis		
Toxicologic	n (%)	
Traumatic	n (%)	
…	n (%)	
Orientation, at discharge from ED (EU patients)		
Return to home	n (%)	
Hospitalization	n (%)	
SSHU	n (%)	
Orientation, at discharge from ED (OU patients)		
Return to home	n (%)	
Hospitalization	n (%)	
Number of falls, within 7 days	n (%)	
Average	mean (SD)	
Number of re-visits to ED for falls, within 7 days	n (%)	
Average	mean (SD)	

Abbreviations: ED: Emergency department; EU: Emergency Unit; OU: Observation Unit; PT: physiotherapy; SD: Standard deviation.

Characteristics of patients at admission to ED will include: gender and age, emergency severity index level, and primary diagnosis.

The primary outcome will be the patient orientation at discharge from the ED according to the defined pathways: return to home (after ERU or SSHU), hospitalization (after ERU or SSHU) or SSHU (after ERU).

The secondary outcomes will be: the length of stay at the ED, or hospital (LOS-ED, LOS-hos) calculated as the duration between admission and discharge from the ED and hospital; the number of re-visits to ED for fall complaints (within 7 days). These outcomes will be found from the medical record of the patient. In addition, a study investigator will call the patient (phone) after 7 days to collect the number of falls since discharge from ED (follow-up).

At the end of the study, the ED medical staff will be asked about their experiences in providing PT within ED: for elderly populations, and in general context. To gather this information, a satisfaction questionnaire containing 4 closed-ended questions, and 2 open-ended questions (for general comments) will be sent electronically via email (Fig 4).

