### Data analysis and interpretation

An independent statistician will perform will perform the analyses (SAS, 9.4^®^).

A review of data will be conducted at the end of the study, prior to statistical analysis. The aim will be to review the progress of the study, potential problems and classify any minor or major deviations. Analyses will be performed in the *Intention-to-Treat* populations corresponding to all randomized patients. A sensitivity analysis will be conducted on the *Per-Protocol* population. This population will include patients without major deviation.

The variables measured at baseline will be described for all patients in both groups by numbers and percentages for each category for categorical variables and the minimum, maximum, average, standard deviation and quartiles for the quantitative variables. (Table 2).

Primary endpoint: the patient orientation at discharge from the ED will be described and compared between the two groups with Chi-square tests, depending on the ED unit of inclusion (emergency unit: 3 modalities: discharge home, hospitalization, observation unit; observation unit: 2 modalities: discharge home, hospitalization).’

Secondary endpoints: LOS-ED and LOS-hos will be described as mean difference and 95% confidence intervals, and compared between the groups using Student’s t tests. The rate of re-visits to ED for fall complaints (characterized as a new episode of fall whose severity requires a re-hospitalization within 7 days) will be compared between groups using Chi-square test. The changes in the patient’s orientation between initial and final decisions will be compared between the groups using Chi-square test. Satisfaction of ED medical staff will be depicted descriptively.

Due to this ‘pragmatic’ approach, it is not possible to compute a priori statistical calculations. The distribution of patients within both units of the ED (EU or UN), the different modalities of patient discharge (Fig 3), and for each group (PT vs no-PT) make it challenging to determine expected differences between groups for the main outcome. As stated, we aim to recruit, as exhaustively as possible, during the inclusion period.

Any missing data will be described and explained. There will be no imputation done on missing data.

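### The primary comparison is valid but unadjusted although plausibly prognostic baseline data are collected, and the direction of change in the initial-to-final decision endpoint is not specified

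*Protocol article*

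**What the plan says.** The Data analysis section of the protocol article fixes the primary method: orientation at discharge is "compared between the two groups with Chi-square tests, depending on the ED unit of inclusion", with three outcome categories for the emergency unit (EU) and two for the observation unit (OU). No covariate is named. The Allocation section adds "The randomization will be not stratified".

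The Outcomes section lists the baseline data: "Characteristics of patients at admission to ED will include: gender and age, emergency severity index level, and primary diagnosis". The initial orientation decision is not in that list. It must be recorded all the same, because the Introduction makes change from the initial to the final physician decision a secondary objective. The Study setting section calls it "an initial decision for patient orientation depending on the clinical severity, treatment requirement, and the initial evolution of the patient" and places it in the first stage of EU care. The readable text does not say whether it comes before or after randomisation.

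For the secondary endpoint, the plan says that changes in "orientation between initial and final decisions will be compared between the groups using Chi-square test". It does not define the categories of change.

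**The concern.** Severity and the early course of the patient inform the initial decision and plausibly also the final one, so the initial decision is a natural baseline measure for this outcome. Age and ESI level are plausible predictors too. The primary test uses none of them. The sample size is a recruitment target with no power calculation behind it, so precision is whatever the enrolled patients give. Covariate adjustment is one of the few ways to improve it without more patients.

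The change endpoint raises a separate question. The Study setting section describes movement both ways: a patient first expected to go home may be admitted, and "if the condition significantly improves with the introduction of treatment, the initial decision for hospital admission can be re-evaluated". These have opposite meanings for the trial's main objective. If the analysis records only whether a decision changed, opposite shifts in the two arms could appear as no difference.

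**Working it through.** **Inputs.** From the protocol: about 336 patients, 1:1, hence 168 per arm; unstratified randomisation; almost 50% of ED visits at age 75 and over followed by hospitalisation (Introduction, a background figure). Assumed here: two-sided 5% level, 50% control rate, one pooled home/hospital outcome, and a binary initial decision split 50/50 and recorded before allocation. The protocol gives no figure for how well the initial decision predicts the final one, so a range is used. The 336 is not derived from power, so there is no statistical figure of the plan to reproduce.

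**Unadjusted precision.** Half-width of the 95% CI for a risk difference = 1.96 × √(2 × 0.25/168) = 0.107, or 10.7 points. Normal-approximation power is 0.45 for 50% against 60%, and 0.80 for 50% against 65%.

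**Closed-form gain.** For two binary variables with 50% margins, φ = 2 × agreement − 1 and R² = φ². Effective N = 336/(1 − R²), and the half-width becomes 10.7 × √(1 − R²).

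| Agreement | R² | Effective N | Half-width (points) |
|---|---|---|---|
| 60% | 0.04 | 350 | 10.5 |
| 70% | 0.16 | 400 | 9.8 |
| 80% | 0.36 | 525 | 8.6 |
| 90% | 0.64 | 933 | 6.4 |

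**Simulation check.** 40,000 runs per setting compared the plain Chi-square with a Cochran-Mantel-Haenszel test stratified on the initial decision. The variance ratio and equivalent N are for the standardised against the crude risk difference. True effect +10 points:

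| P(final home), initial home / not home | Power, unadjusted | Power, stratified | Variance ratio | Equivalent N |
|---|---|---|---|---|
| 0.6 / 0.4 | 0.47 | 0.47 | 0.96 | 348 |
| 0.7 / 0.3 | 0.47 | 0.52 | 0.84 | 399 |
| 0.8 / 0.2 | 0.47 | 0.62 | 0.66 | 510 |
| 0.9 / 0.1 | 0.47 | 0.83 | 0.41 | 825 |

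For +15 points, power is 0.81 unadjusted, against 0.81, 0.86, 0.93 and 0.99 stratified. With no effect, rejection rates are 0.054 to 0.058 unadjusted and 0.048 to 0.050 stratified, so both tests are close to nominal.

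**Effect of the split by unit.** The planned tests are run within units, so neither uses all 336 patients. An even split (assumed) leaves 84 per arm and a half-width of 1.96 × √(2 × 0.25/84) = 0.151, or 15.1 points. Unit of inclusion already carries part of the triage information, so the further gain within a unit may be smaller than the tables show.

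**Direction.** Illustrative counts, 168 per arm:
- Coded changed/unchanged, 34 against 34 changed: Chi-square 0.0, p = 1.0.
- The same patients coded by direction, 26 towards home, 8 towards hospital and 134 unchanged against 8, 26 and 134: each of the four change cells has expected count 17, so Chi-square = 4 × 9²/17 = 19.06 on 2 df, p = 0.00007.

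**The case against.** The strongest reply is that an unadjusted Chi-square is valid under this randomisation, and that covariates and endpoint coding are ordinary content of an analysis plan, which is not shown. The first part stands. The second stands only in part: the article does not leave the primary method open but names a test that takes no covariate, so changing it means changing stated text.

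Several stronger readings are tempting, and the documents do not support them.

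- A reader might infer that changes will be counted without direction. The text leaves the coding open, and a Chi-square test accepts directional categories; the plan itself uses three categories for EU patients. Nor would direction be wholly hidden, because a net shift between arms would show in the primary table.
- A reader might infer that much precision is certainly being lost. No agreement figure is given, and for some OU patients the initial decision may simply have been observation, which says little about home against hospital.
- A reader might treat the initial decision as an established baseline variable. It is absent from the list of admission characteristics, and the readable text does not place it before allocation. In an open-label trial that order matters.
- A reader might treat 336 as fixed. The protocol says recruitment may result in that number, aims to recruit as exhaustively as possible, and allows the period to be extended.

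**Conclusion.** The point holds as an inefficiency in the primary analysis and an unspecified direction in one secondary endpoint. It is not an error in the primary test. The gain from using the initial decision is unknown: equivalent to roughly 350 patients instead of 336 if prognosis is weak, and to about 400 to 900 if it is moderate to strong. Those figures rest on a 50% rate, a pooled binary outcome that the plan does not use, and an initial decision recorded before allocation. The gain from age and ESI level was not calculated. The cancellation example shows what a changed/unchanged coding could do; it does not show that this coding is planned.

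**What to change.** 1. Keep the stated outcome categories by unit of inclusion. Collapsing them to home against hospital would drop the EU category of transfer to observation and change the endpoint.
2. Make the primary comparison a regression on arm adjusted for age and ESI level: multinomial for the three EU categories, logistic for the two OU categories. Report marginal risk differences with 95% CI.
3. Make the initial physician decision a required field before the web system releases the allocation. Use it as a covariate only where it was recorded before allocation was revealed.
4. Define the change endpoint by arm as towards home, unchanged or towards hospital.

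The cost is some analysis wording, slightly more analysis work and one field in the randomisation system; no patient is asked for anything more. One limit remains. The study window opens on 6 April 2023 and the flowchart cites protocol version 2 of June 2023, so patients enrolled before the field is added may lack a verified pre-allocation decision. For them, adjustment rests on age and ESI level alone, and the plan should say how the two sets of patients are combined.

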### Ethical considerations and data management

This study and all of its components were approved by local Ethics committee (GNEDS, n° 23-30-02-230, date: February 23, 2023). The protocol of the trial was also registered with the US National Institute of Health database (NCT05753319). The study protocol approved by the Ethics committee is provided in S4 File (english version and original version).

Data will be logged in anonymous data sheets, accessible and stored electronically on a password-protected software (ENNOV Clinical). Only researchers will be allowed to access to the data. The software enables the identification of individuals who logged in and their actions, so as to restore different document versions. Data will be stored Nantes hospital-university centre for 15 years after completion of the study. Coded data and statistical scripts will also be stored for archiving purposes.

Individual data will not be shared (or only without identification, i.e. coded) for primary and secondary outcomes in publication, in an open archive repository (HAL). According to the European Union General Data Protection Regulation and French laws, each participant will be aware on their rights: to access, rectify and erase their personal data, so as the right to data portability. We do not plan to transfer data outside the EU countries.

## Discussion

### Originality and performance of the study

The results of this study will address existing gaps in the literature, by investigating the effects of PT in ED settings, with a particular focus on falls complaints. We aim to provide comprehensive answers to better understand the extent to which the delivery of PT might improve patient outcomes for elderly populations, who are major users of ED.

Moreover, the study will focus on the perceptions of the medical staff and identify barriers and facilitators to PT within ED. These results will also provide results favouring the dissemination of the results and influence current practices.

### Issues related to recruitment

The use of ED is very popular by populations aged 75 years and over for fall complaints. The inclusion criteria aim to facilitate the recruitment within ED, for this study. We anticipate our recruitment flow to be relatively smooth. Any recommendations to the DMC might be made to modify recruitment if judged necessary. The recruitment status will be reviewed every 2 months to determine the likelihood of meeting recruitment timeline. If recruitment is slower than expected, the recruitment period will be extended until recruitment is successfully concluded.

### Issues related to trial design

This study uses a pragmatic approach aimed at reflecting and informing clinical practice.

Elderly populations were not involved as patient-partners. The objectives and outcomes of this research were defined according to the literature and clinical expertise among investigators. The study design also took into consideration the practical aspects of ED, and its inherent challenges, including professional overuse. Given these circumstances, it seemed reasonable to structure the trial in a way that seamlessly integrates into the regular functioning of the ED.

We should carefully ensure that the study might not disrupt or interfere with standard patient care, and aligns with the day-to-day operations of the ED. Our approach aimed to capture the authentic conditions and demands of the ED environment while conducting the trial. In this specific setting, it would appear that the measurements other risk factors for falls (e.g., muscular performance, sensory disturbances, reduced visual acuity, [45]), or the use of standardized batteries (e.g. BESTest, which requires time/equipment for administration) could not be measured in a pragmatic study of the almost usual care in the ED. Information about patients’ medications is also incomplete when patients arrive at the ED, and would appear to be challenging to collect in the present study.

### Issues related to adverse events

A serious adverse event related to this study would be a fall during the delivery of PT. Investigators may report any adverse event (with or without an expected relationship with the intervention) to the study coordinator. If so, a report to the data monitoring committee (DMC) will be made by the investigators. Appropriated care within the ED will be provided in case of adverse event and for post-trial care, if judged necessary. It Is within the scope of the DMC to communicate to relevant parties (e.g., investigators, Ethics committee) if necessary.

### Monitoring and auditing

The study was designed by clinicians and researchers from complementary fields: emergency medicine, rehabilitation sciences, and biostatistics, from the ED, the Hospital, and the School of Medicine. These members will compose the DMC. Each two month, the role of the DMC will be to examine the flow of recruitment, examine potential adverse events, and make recommendations to protect participants’ safety and protocol modifications (e.g., changes in eligibility criteria, outcomes or planned analyses). The analyses will be performed by the trial statistician. An external auditing will be made at mid-recruitment and at the estimated date of study completion, involving peers’ researchers from the Hospital and the University, familiar with the ED, but not affiliated with the project. This audit will confirm that the regulatory binder is complete and that all associated documents are up to date.

### Dissemination

The results of this study will be disseminated to through our and neighbouring EDs, and through professional emergency and physiotherapy networks and faculties (e.g., lectures). We will also apply to present the trial results at conferences among these fields. Scientific written reports of the findings will conform to the Consolidated Standards of Reporting Trials (CONSORT) statement guidelines. The publication authorship will be determined based on the International Committee of Medical Journal Editors (ICMJE) guidelines. We intend to publish in a reputable non-predatory journal, selecting the most relevant one in using emergency and/or physiotherapy related-categories based on SCImago Journal ranking. We may also considerate the necessity of engaging a professional medical writer.
